### Recruitment {15}

We have done an analysis of case numbers presenting at the 8 included hospital sites and believe that the numbers available for recruitment exceed required numbers by 50%.

If recruitment is too slow to enable recruitment of the whole sample over 12 months, then we plan to add further centres in Ethiopia.

Our patient information leaflet has been translated into all relevant local languages. The site PIs have been educated regarding the rationale for the study and the informed consent process. They have cascaded education to their departments.

Consenting patients will be offered a small stipend to support attendance at follow-up visits.

## Assignment of interventions: allocation

### Sequence generation {16a}

Randomisation will be computer generated block randomisation to ensure equal numbers over the intended sample size of 220 patients. Randomisation will be stratified according to the Gartland 2b (rotational displacement only) and Gartland 3 (total off-end displacement) fractures as these are seen to represent separate patient sub-groups.

Ensuring equal numbers of each of these two sub-groups in each treatment arm will eliminate bias based on injury severity characteristics.

### Concealment mechanism {16b}

Following consent, the PIs will access the randomisation online, giving complete concealment.

### Implementation {16c}

The computer generation of the block randomisation will be controlled by the study overseer [name] [name]. Patients will be enrolled by the site PIs and their surgeon teams; application of treatment modality following randomisation will be by the local treating surgeon teams.

## Assignment of interventions: blinding

### Who will be blinded {17a}

The participants and care providers will not and cannot be blinded as there is an obvious visible difference between the non-operative LSAT and operative CRPP treatments.

The scoring technicians who administer the primary outcome PROMIS UE questionnaire and the secondary outcome PROMIS 7 + 2 will be blinded to which treatment the patient received. This scoring will be done by telephone, and the technicians are not part of the treating team, so at no point see the patient. They will be required not to ask which treatment was received, and to request the guardian not to volunteer which treatment had been received.

The study data analyst will also be blinded as to which treatment arm is which when analysing the results.

### Procedure for unblinding if needed {17b}

There is no instance where the scoring technicians may be required to unblind.

The treating teams are not blinded at any point and can therefore intervene for any complications or issues based on normal clinical judgement.

## Data collection and management

### Plans for assessment and collection of outcomes {18a}

The primary outcome measure is the PROMIS Pediatric Parent Proxy Short Form Upper Extremity version 3.0. At analysis, this score will be analysed as a mean for each group, and the Minimum Clinically Important Difference of 3.5 points will be applied to assess for inferiority of one or the other treatment modality.

Furthermore, we will analyse the range of scores to understand the distribution of negative outliers in each group who may have had a particularly poor outcome. This range will also be presented in the results.

The secondary outcome includes the PROMIS Parent proxy Global Health 7 + 2 PROM.

These two PROMIS will be administered by telephone to parents of the children, and data filled contemporaneously with the answers will then be entered into the STOPUS web database. The total scores will be converted into T scores according to the specific PROMIS converter tables validated for each score. The telephone scoring technicians will be specifically trained to do the PROMIS scores by telephone.

Complication data will be measured against a checklist by treating surgeons trained to assess complications. Findings will be entered by surgeons to the STOPUS database.

Parent satisfaction visual analogue scale will be scored by pointing to a laminated sheet and the score entered by the surgeon to the electronic STOPUS database.

The Flynn’s criteria will be measured using a goniometer by surgeons trained for this, and the findings will be entered to the STOPUS electronic database.

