### Objectives {7}

To test if LSAT is non inferior to CRPP as measured by the PROMPROMIS Parent Proxy Upper Extremity – Short Form 8av3.0 at 12 months after injury, and in the LMIC context.To assess Global Health at 6 and 12 months using PROMISParent Proxy Global Health 7+2 v3.0To assess complications of both LSAT and CRPPEconomic evaluation to compare hospital-based costs for LSAT and CRPPTo compare elbow function by Flynn’s criteria 3 months after LSAT/CRPP To compare guardian satisfaction with treatment by LSAT/CRPP 

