### Sample size {14}

Power analysis has been performed to determine the sample size required for a non-inferiority study based on the PROMIS Upper extremity parent proxy short form 8a version 3.0 score primary outcome, with the Mean Clinically Important Difference MCID set at 3.5 to detect clinically significant differences between the two treatment groups. Initial calculations suggest 202 patients would be required (101 per group). We will aim to recruit 222 patients to the study, leaving a 10% margin of error to account for loss to follow-up. Patients will be randomly assigned to either the straight arm traction group (Group 1) or the operative treatment group (Group 2) using a computer-generated randomisation sequence. Allocation concealment will be maintained to ensure blinding.

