## Statistical methods

### Statistical methods for primary and secondary outcomes {20a}

The data analysis will be conducted by a statistician who is blind to the treatment groups and has not been part of the clinical study.Analyse the primary outcome using appropriate statistical methods, such as linear mixed-effects models or generalised estimating equations, adjusting for baseline functional status and potential confounders. The means of the 12-month PROMIS UE Proxy score will be used for assessing a difference above the MCID. Range analysis, including negative outliers, will also be assessed and presented in the results.Report estimated treatment effects.Compare the incidence of complications between treatment arms using appropriate statistical tests (e.g. chi-square test, Fisher’s exact test).Calculate relative risks or odds ratios for complications between treatment arms with corresponding confidence intervals.Explore potential treatment effect modification by conducting subgroup analyses based on relevant patient characteristics (e.g. age, fracture severity).Evaluate for interaction effects between treatment assignment and subgroup variables.

Missing data handling:Assess the extent of missing data and explore reasons for missingness, particularly for outcome variables.Utilise appropriate methods for handling missing data, such as multiple imputation or sensitivity analyses, to assess the robustness of results.Over-recruit by 10% case numbers above the power calculation to mitigate for missing data.

Sensitivity analyses:Perform sensitivity analyses to examine the impact of different assumptions or analytical approaches on study results (e.g. excluding patients with incomplete follow-up, adjusting for potential confounders).We intend to analyse and present results according to ‘intention to treat’ but will also undertake and present an analysis of ‘actual treatment’.

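### The 3.5-point margin is applied to group means with no confidence limit tied to it, which does not test the stated non-inferiority objective

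*Protocol article*

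**What the plan says.** The objective is one-directional: "To test if LSAT is non inferior to CRPP" on the PROMIS Parent Proxy Upper Extremity score at 12 months (Objectives {7}; the research question in Background and rationale {6a} has the same direction).

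The use of 3.5 points is described in three places:

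- **Sample size {14}** refers to a power analysis for a non-inferiority study, "with the Mean Clinically Important Difference MCID set at 3.5 to detect clinically significant differences between the two treatment groups". It gives 202 patients (101 per group), raised to 222.
- **Plans for assessment and collection of outcomes {18a}** has each arm summarised by its average, after which "the Minimum Clinically Important Difference of 3.5 points will be applied to assess for inferiority of one or the other treatment modality".
- **Statistical methods {20a}**: "The means of the 12-month PROMIS UE Proxy score will be used for assessing a difference above the MCID".

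Statistical methods {20a} also offers mixed models or generalised estimating equations for the primary outcome. For reporting, its instruction is "Report estimated treatment effects". Confidence intervals are named only for complications: "Calculate relative risks or odds ratios for complications between treatment arms with corresponding confidence intervals".

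**The concern.** A non-inferiority claim needs the data to rule out a deficit as large as the margin, so the margin has to be compared with a confidence limit. The two analysis passages instead look for a difference above 3.5 between means. Not finding one is different from excluding one: an observed deficit just under 3.5 is compatible with a true deficit well above it.

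The Abstract says that a non-inferior result would support treating children locally with LSAT. If the rule were applied as worded, that conclusion would carry no controlled error rate.

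**Working it through.** **Inputs from the protocol article.** Margin 3.5 points, 101 per group, equal allocation, T-score outcome.

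**Assumptions.** The article gives no SD, alpha or power. I use SD 7 to 12, one-sided alpha 2.5% or 5%, a normally distributed mean difference d (LSAT minus CRPP), and a higher score meaning better function.

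**1. The plan's own figure.** n per group = 2 × SD² × (z_α + z_β)² / 3.5².
- SD 10, one-sided 5%, 80% power: 2 × 100 × (1.645 + 0.842)² / 12.25 = 100.9, so 101.
- SD 8.87, one-sided 2.5%, 80% power: 2 × 78.68 × (1.960 + 0.842)² / 12.25 = 100.8, so 101.

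Both give 202 in total, and 202 × 1.10 = 222. The figure is attainable, but the article does not show which inputs produced it.

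**2. Literal rule: pass if d > -3.5.** SE = SD × √(2/n). At a true difference of -3.5,

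P(pass) = 1 - Φ((-3.5 + 3.5)/SE) = 1 - Φ(0) = 0.50.

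SE cancels, so this holds for any SD and n. It needs only an unbiased, roughly symmetric estimate. The version that looks both ways, |d| < 3.5, also gives 0.50 to the precision shown (SD 7 to 12, 91 to 111 per group).

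**3. Larger true deficits, SD 10.** SE = 10 × √(2/101) = 1.407. The 95% rule passes if d - 1.96 × SE > -3.5.

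| True deficit | Means-only rule | 95% confidence-limit rule |
|---|---|---|
| 3.5 | 50% | 2.5% |
| 4.0 | 36% | 1.0% |
| 4.5 | 24% | 0.4% |
| 5.0 | 14% | 0.1% |

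At a true deficit of 4.5 the means-only rule passes LSAT 15.5% of the time with SD 7 and 27.7% with SD 12.

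**4. A single result, SD 10.** An observed deficit of 3.4 has a 95% interval of -3.4 ± 1.96 × 1.407, that is -6.2 to -0.6. The means-only rule accepts it, although LSAT is significantly worse and a deficit of 6 is not excluded.

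**5. Largest observed deficit that passes a confidence-limit rule.** For the two designs in step 1:
- SD 10 with a 90% interval: 3.5 - 1.645 × 1.407 = 1.19 points.
- SD 8.87 (SE 1.248) with a 95% interval: 3.5 - 1.96 × 1.248 = 1.05 points.

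The means-only rule allows anything up to 3.5.

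**6. The significance reading.** If LSAT fails only when the data show significantly that its deficit exceeds 3.5, then at a true deficit of 3.5 it fails 2.5% of the time at one-sided 2.5%. It therefore passes about 97.5% of the time.

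**The case against.** The best reply is that the text names a summary measure (means) and a threshold (3.5) and leaves out the inferential step. It never says that non-inferiority will be claimed when the observed difference is below 3.5. A power analysis for non-inferiority presupposes an alpha, and the planned models produce a standard error and an interval. Interval level and sidedness are often left to a full protocol or SAP, and neither is shown.

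Part of this stands. The article does not exclude a confidence interval, so a reader who infers that 50% is the trial's established false-claim rate goes further than the text; it follows from the literal reading only. Silence on alpha alone would be no finding. What remains is that the article does describe how 3.5 is used, twice, and both descriptions look for a difference, in conflict with its own objective.

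Two other inferences are not supported:

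- **That the reference to either arm causes the error.** It does not: the one-sided and two-sided forms both give 50%. The wording may simply reflect the analyst being blinded to which arm is which (Who will be blinded {17a}).
- **That the trial is underpowered.** With 101 per group, SD 10 and a 95% interval, power is Φ(3.5/1.407 - 1.96) = Φ(0.527) = 70%. That needs both assumptions together. With SD 8.87 and a 95% interval, or SD 10 and a 90% interval, power is 80%. No shortfall is shown.

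**Conclusion.** The point holds as a badly worded decision rule. The two analysis passages compare means with the margin and tie no confidence limit to it, which contradicts the non-inferiority objective. On the literal reading the false-claim rate at the margin is 50% irrespective of SD and sample size; on the significance reading it is higher. A confidence-limit rule gives 2.5% or 5%, depending on the level chosen. The rates for deficits beyond 3.5 depend on the assumed SD. It should be corrected because it governs the trial's main conclusion.

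**What to change.** In Plans for assessment and collection of outcomes {18a} and Statistical methods {20a}, replace the comparison of means with one rule: LSAT is non-inferior to CRPP if the lower confidence limit for the adjusted 12-month mean difference (LSAT minus CRPP) lies above -3.5 T-score points. Add that the non-inferiority claim is directional for LSAT. A coded analysis can still be run both ways while the analyst is blinded.

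Match the confidence level to the alpha behind the 202 patients: two-sided 95% for one-sided 2.5%, or two-sided 90% for one-sided 5%. In Sample size {14}, state the SD, alpha and power that were used, so that the match can be checked.

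The cost is wording only, with no new data. The stated power may become less favourable: if the 202 rested on SD 10 and one-sided 5%, choosing a 95% interval lowers it from 80% to 70%.

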A supracondylar fracture is a break in the humerus (upper arm bone) occurring up to two inches (5 cm) above the elbow joint. The condyles of the humerus are the two rounded prominences at the end of the bone that are part of the elbow joint. Supracondylar fractures are the most common form of elbow fracture in children, with an annual incidence between 60 and 177 per 100,000 children [1, 2]; these fractures are rare in adults. Supracondylar elbow fractures can occur throughout childhood but are most common in children between 5 and 6 years of age [3]. Several epidemiological studies have reported little gender difference in the incidence of these injuries [1–3]. The typical mechanism of injury is a fall onto an outstretched hand or less commonly a direct fall onto a flexed (bent) elbow [4]. Only 1% of supracondylar fractures are open, with an associated wound providing a direct route for contamination of the bone ends; the remaining 99% are closed (with no open wound). Open fractures require urgent surgical treatment to reduce the risk of serious infection [1]. Successful treatment of a supracondylar elbow fracture in a child leads to normal function with no lasting disability. However, complications of this injury can occur because of the initial injury or because of problems during treatment. The major blood vessels and nerves in the arm can be damaged during the injury, the operation, or because of compartment syndrome. The last mentioned is a rare complication where there is excessive swelling in the arm, increasing pressure in the arm, and compressing the small blood vessels; this can cause permanent damage to the muscles and nerves if not identified and treated promptly. The other significant complication relates to the alignment of the arm. This can arise because of malunion (the bone healing up in the wrong position after injury), or because of altered growth around the elbow. Children may end up with an arm with cubitus varus (the forearm pointing towards the midline), cubitus valgus (excessive bending away from the midline), or rotational abnormalities. Cubitus varus is commonly unsightly and can be associated with reduced function of the limb. To identify and try to prevent these serious complications, an adequate history and examination to identify nerve or blood vessel compromise are essential when assessing children with this fracture. Clinical findings along with fracture pattern and the degree of displacement on x-ray can be used to predict the risk of complications. In displaced supracondylar fractures, the reported rate of vascular injury ranges from 5 to 31% and nerve injury at presentation from 5 to 15% [2–5]. Ninety-five per cent of supracondylar fractures are extension-type injuries, where the elbow has been over-extended, and the elbow moves backwards in relation to the humerus. Five per cent are flexion type injuries, where the elbow has been over-bent, and the elbow has been pushed forwards in relation to the humerus; these are typically more unstable and more challenging to treat. There are two commonly used classifications for describing the radiographic appearance of supracondylar fractures. The Gartland classification has been used extensively to describe these injuries and is useful for identification of type I (undisplaced) and type III (completely displaced) fractures [6]. Type II fractures (intact posterior cortex) may rotate or have angulation and therefore represent a heterogeneous group of fractures. The Gartland classification has been modified to further describe type II fractures based on the presence of rotation [7] and expanded to include fractures with no intact periosteum. Alternatively, the Arbeitsgemeinschaft für Osteosynthesefragengroup (German for Association for the Study of Internal Fixation) or AO classification offers improved clarity in describing the expected stability of these fractures [8].

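### The range of 12-month scores cannot show how many children did badly, so a moderate excess of poor scores could sit behind a non-inferior mean

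*Protocol article*

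**What the plan says.** Under Plans for assessment and collection of outcomes {18a}, the primary outcome is handled in two steps. First, the arms are compared on their average score: "the Minimum Clinically Important Difference of 3.5 points will be applied to assess for inferiority of one or the other treatment modality". Second, as an addition, "we will analyse the range of scores to understand the distribution of negative outliers in each group", with the aim of identifying children whose result was particularly poor. The reported statistic is named: "This range will also be presented in the results".

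Statistical methods {20a} repeats the plan: "Range analysis, including negative outliers, will also be assessed and presented in the results".

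Neither section defines a negative outlier or a poor score. Neither plans to count such children per arm or to compare the counts.

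The Background {6a} gives the clinical setting: "Successful treatment of a supracondylar elbow fracture in a child leads to normal function with no lasting disability". It then describes complications that can leave permanent damage. So a failed treatment may appear as a low tail of scores and not as a small shift in every child.

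**The concern.** The aim is sound, because a mean can hide a minority who do badly. The statistic chosen does not meet it. A range is set by the highest and the lowest child in each arm. If many children score near the top of the scale, the upper ends will be similar, and what the range says about poor results comes down to the single lowest child per arm. One very poor result and a dozen equally poor results give the same range.

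At stake is how a non-inferior mean is read. The Discussion in the abstract says such a result would support treating children locally with traction. Readers would want to know whether it came with more badly affected children, and the planned description could not tell them.

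**Working it through.** **1. The plan's own figure.** Sample size {14} gives 202 (101 per group) for a margin of 3.5, but no SD, alpha or power, so 202 cannot be reproduced. Solving n = 2·SD²·(z(1−α) + z(power))²/3.5² backwards for n = 101, with a true difference of 0, gives the SD each design would imply. If non-inferiority is judged by a confidence limit (an assumption), the largest observed deficit that still passes is 3.5 − z(1−α)·SD·√(2/101), with √(2/101) = 0.1407.

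| One-sided α | Power | Implied SD | z·SD·0.1407 | Largest passing deficit |
|---|---|---|---|---|
| 0.025 | 80% | 8.88 | 2.45 | 1.05 |
| 0.025 | 90% | 7.67 | 2.12 | 1.38 |
| 0.05 | 80% | 10.0 | 2.31 | 1.19 |
| 0.05 | 90% | 8.50 | 1.97 | 1.53 |

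**2. What excess of poor scores fits inside that.** If poorly recovered children score D points below the rest (D is assumed), an excess proportion e lowers the mean by e·D. So e = passing deficit / D:
- D = 10: 1.05/10 to 1.53/10, or 10.5 to 15.3 percentage points
- D = 15: 7.0 to 10.2
- D = 20: 5.3 to 7.7
- D = 25: 4.2 to 6.1

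**3. A worked case.** Assume scores are either 50 or 30, with 1 of 101 poor under CRPP and 11 of 101 poor under LSAT.
- Ranges: 50 − 30 = 20 in both arms.
- Mean difference: −20 × 10/101 = −1.98.
- SE = √((39.2 + 4.0)/101) = 0.65. Lower 95% limit = −1.98 − 1.972 × 0.654 = −3.27, which is inside the margin.
- Fisher's exact test on 1 against 11: p = 0.005.

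The excess here is 9.9 points, above the 5.3 to 7.7 in step 2 for D = 20. The reason is that the two-value scores are less spread (SD about 0.654/0.1407 = 4.6) than the SDs in step 1.

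**4. Direction alone.** If one arm has 10 poor outcomes and the other 5, with the same severity distribution, the arm with twice as many holds the lowest score with probability 10/15 = 67%.

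**5. Simulation.** Assumptions: 10,000 trials, 101 per arm, a 20-point shortfall, scores limited to 15 to 57, a poor score defined as below 35, and SD 5 or 8.8 before the shortfall. Each pair below is for SD 5 and SD 8.8.

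| True poor, CRPP vs LSAT | Non-inferiority met | Power, ranges | Power, proportion below 35 |
|---|---|---|---|
| 5% vs 10% | 71%, 54% | 4%, 4% | 23%, 13% |
| 5% vs 15% | 31%, 24% | 6%, 6% | 59%, 33% |
| 5% vs 20% | 7%, 7% | 7%, 6% | 87%, 59% |

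Across all the excess scenarios simulated, a calibrated comparison of ranges had 4 to 10% power, against 13 to 87% for the proportion.

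**6. Precision of the alternative.** At 5% vs 15% and 101 per arm, the 95% half-width is 1.96·√((0.05·0.95 + 0.15·0.85)/101) = 8.2 percentage points.

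**The case against.** The strongest reply is that this is a descriptive supplement. It is not a listed outcome or a decision rule. The text speaks of a distribution and of outliers in the plural, so the authors may intend to show every low score. A cut-point and a table could also be left to an analysis plan that is not shown. The first part stands: nothing is decided on the range, and no wording forbids a fuller display. But the protocol does more than leave detail open. It names a statistic in two places, and that statistic cannot do the stated job.

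A reader might infer that an excess of badly affected children would go undetected altogether. The documents do not support that. Complications, including nerve injury, arterial compromise and Volkmann contracture, are compared formally with relative risks or odds ratios and confidence intervals. Flynn's criteria are measured in each child, and the same PROMIS score is also taken at 6 months. These limit the gap without closing it. Complications and Flynn's criteria are assessed by 3 months by treating surgeons who know the allocation, and Interim analyses {21b} says recovery may be slower with LSAT. The 12-month score is the only planned measure of upper limb function at that time.

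A reader might also infer that the margin lets through excesses of 3.5/10 = 35, 3.5/15 = 23, 3.5/20 = 17.5 or 3.5/25 = 14 percentage points. That treats a full 3.5-point deficit as passing. The trial is sized for non-inferiority. Under a confidence-limit test, a true deficit of that size passes only at the alpha rate, and the observed deficit must be 1.05 to 1.53, which is 30 to 44% of it. Large excesses mostly fail on the mean: 5% vs 20% met non-inferiority in about 7% of simulated trials.

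Finally, the proportion is itself imprecise at this sample size. That stands.

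**Conclusion.** The point holds in a limited form. The range is the wrong statistic for the stated aim, because its lower end is one child per arm and it does not count poor results. An observed excess of roughly 4 to 15 percentage points of poor 12-month scores could accompany a non-inferior mean and not show in the range.

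That span rests on assumptions that the documents do not supply: a shortfall of 25 down to 10 points, an SD of about 7.7 to 10 inferred from 101 per group, and a confidence-limit test of non-inferiority. The base rates, scale limits and cut-off of 35 in the simulation are also assumed. The primary comparison is not made wrong by this. What is lost is a usable description of the low tail. It is worth correcting because the correction is cheap.

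**What to change.** In sections {18a} and {20a}, replace or supplement the range analysis with a supportive analysis fixed before unblinding:
- the number and proportion of children per arm with a 12-month T-score below a prespecified cut-point;
- the risk difference with a 95% CI, stratified by Gartland type as the randomisation is;
- the cumulative distribution of 12-month scores by arm.

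A cut-point of 40 is one example: one reference SD below 50 if the standard T-score metric applies. The protocol does not state that metric, so the sponsor must justify the value.

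The cost is analysis wording and one choice of cut-point. No extra data or patients are needed. With a half-width of about 8 percentage points at about 101 per arm, the analysis should be labelled supportive and not definitive.
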